#### *Tumor biopsy acquisition*

- Fine-needle aspiration, brushing, cell pellet from pleural effusion, and lavage samples are not acceptable.
- For core needle biopsy specimens, at least two cores (maximum four cores) should be submitted for evaluation at each biopsy (pre-treatment and on-treatment). Details for

acquiring, processing, storing, and shipping these samples will be provided in the Laboratory Manual.

- At the University of Colorado only, two additional core biopsies should be obtained at the pretreatment biopsy. These should be immediately placed into a provided specimen cup with RPMI. The container should immediately be brought to the [name] lab for injection into mice. This process has been approved by the Institutional Animal Research Committee.

Safely biopsied disease is defined as:

- cutaneous lesions (without evidence of active infection)
- peripherally accessible lymph nodes (cervical, axillary, inguinal, extremities)
- liver metastases (not immediately adjacent to major vessels)
- lung metastases easily accessible by percutaneous biopsy or endobronchial ultrasound
- rectal lesions

Lesions not allowed for biopsy include brain, mediastinum, pelvis, or any lesion deemed by the patient's primary oncologist, study investigator, or radiologist to represent greater risk to the subject.

If non-evaluable tumor tissue is collected from the on-study biopsy procedures, (e.g., necrotic or fibrotic tissue, or the procedure is interrupted because of a complication), the patient will still be eligible to continue treatment.

#### *Tumor biopsy assessments*

Tumor tissue will be assessed using 9-color multispectral imaging and mRNA expression.

#### Nine-color multispectral imaging

The frequency and activation status of infiltrating immune cells in the tumor microenvironment will be compared before and after treatment using 9-color multispectral imaging. Through our collaboration with the Human Immune Monitoring Shared Resource (HIMSR) at the University of Colorado School of Medicine we will phenotype, quantify, and determine the spatial relationship of immune infiltrate in formalin-fixed paraffin-embedded biopsies. We will determine the presence and activation status of myeloid and lymphoid cells in the tumor microenvironment, determine the level of inhibitory markers (CD47, PD-1, and PD-L1), and measure EGFR expression on tumors by staining slides from untreated and treated biopsy specimens with antibodies. Mismatch repair status will also be assessed at baseline.

After staining, whole slide scans will be collected using the 10x objective and approximately 20 regions of interest covering the entire tissue biopsy will be selected. Multispectral images of each region of interest will then be collected using the 20x objective with a 0.5-micron resolution. The 9-color images will be analyzed with inForm software to segment the tissue and

compare the frequency and location of immune cell infiltrate in tumor and stromal areas, to phenotype the cells according to morphology and cell marker expression, and to score each cell for expression of activation and inhibitory molecules. The frequency of each immune cell subset, the activation status of those subsets, the expression of inhibitory molecules, and their location relative to tumor regions in post-treatment biopsies will be compared to the baseline biopsy in each patient to determine whether treatment with evorpacept (ALX148), cetuximab, and pembrolizumab reprograms the tumor microenvironment. The pre- and post-treatment biopsies will also be compared between patients that respond to treatment and patients that are refractory to treatment.

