EGFR can be qualitatively measured using immunohistochemistry (IHC). While fast and cheap, it is an inconsistent method (inherent subjectivity of interpreting results and results are dependent on the antibody used). EGFR is expressed in up to 80% of patients with CRC. However, multiple studies have failed to demonstrate a correlation between EGFR expression by IHC and anti-EGFR efficacy (targeting EGFR signaling pathways), including some patients who respond to anti-EGFR therapy with undetectable EGFR by IHC. Therefore EGFR IHC (or by other methods) is not used or recommended in clinical practice to select patients for anti-EGFR therapy (targeting EGFR signaling pathways) or to predict response. In this present study, EGFR expression will be evaluated as an exploratory endpoint.

---

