### 6.3 MEASURES TO MINIMIZE BIAS: RANDOMIZATION AND BLINDING

There is no randomization or blinding in this study.

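### The imaging operator is not masked to time point or response when biopsy regions are selected and analysed, which leaves the exploratory paired tissue analysis open to an avoidable bias of unknown size

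*Protocol*

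**What the plan says.** Section 6.3, the section on measures to minimize bias, consists of one statement: "There is no randomization or blinding in this study".

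Section 8.2.6 (nine-color multispectral imaging) sets out the tissue workflow. Whole-slide scans are taken, and then "approximately 20 regions of interest covering the entire tissue biopsy will be selected". "The 9-color images will be analyzed with inForm software to segment the tissue and" compare immune infiltrate in tumor and stroma, to phenotype the cells, and "to score each cell for expression of activation and inhibitory molecules". Each patient's post-treatment biopsy is compared with the baseline biopsy. In addition, "The pre- and post-treatment biopsies will also be compared between patients that respond to treatment and patients that are refractory to treatment".

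The section does not say who selects the regions, gives no selection rule beyond whole-biopsy coverage, and does not mention masking to visit or outcome. Where it refers to the Laboratory Manual, it does so for obtaining, processing, storing and shipping samples, not for reading images.

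Section 9.4.8 plans a two-sided paired t-test at alpha 0.05 on the change in immune cells. It states 81% power with 18 pairs for a mean difference of 5% and an SD of differences of 7%, and raises Cohort A to 23 to allow for losses. Section 9.1 gives directional exploratory hypotheses: a stronger immune response after treatment than before (hypothesis 2), and in responders than in non-responders (hypothesis 3).

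**The concern.** Treatment cannot be masked in a single-arm trial, but the reading of a slide can be. Here someone still chooses about 20 fields per biopsy and runs the image analysis. As written, that person may know which slide is pre-treatment, which is on-treatment and, depending on when slides are read, whether the patient responded. The hoped-for direction is stated in the protocol.

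A paired pre/post test without a control group cannot separate a treatment effect from a consistent difference in how the two sets of slides are handled, because both appear in the mean paired difference. Knowledge of response could bias the responder comparison in the same way.

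What is at stake is whether the tissue result can be interpreted. The endpoints are exploratory, but the paired analysis fixes the size of Cohort A, and it is the reason patients in that cohort undergo two research biopsies.

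**Working it through.** **Inputs.** From Sections 9.2 and 9.4.8: 18 evaluable pairs (Cohort A 23), assumed mean paired difference 5 percentage points, SD of differences 7, two-sided paired t-test, alpha 0.05. The protocol gives no figure for a systematic handling difference, so shifts of 1, 2 and 3 points are assumed to show the range.

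**Formula.** With n pairs and a mean paired difference d, the noncentrality is λ = d / (SD/√n). The rejection probability is P(T > c) + P(T < −c), where T is noncentral t with n − 1 degrees of freedom and noncentrality λ, and c is the 97.5% point of the central t.

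**Step 1: reproduce the stated power.** For n = 18, SD/√n = 7/4.243 = 1.650 and c = 2.110 (17 df). With d = 5, λ = 5/1.650 = 3.03 and the power is 81.5%, in agreement with the stated 81%. With all 23 patients evaluable it would be 90.5%.

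**Step 2: smallest significant mean change.** This is c × SD/√n = 2.110 × 1.650 = 3.5 points at n = 18, and 3.0 points at n = 23.

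**Step 3: no true change, but a constant shift b between pre- and on-treatment slides.** Put d = b and keep SD at 7.

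| Assumed shift b (points) | λ at n = 18 | Chance of a significant result, n = 18 | Same, n = 23 |
|---|---|---|---|
| 0 | 0 | 5% | 5% |
| 1 | 0.61 | 8.8% | 10.1% |
| 2 | 1.21 | 20.8% | 25.9% |
| 3 | 1.82 | 40.4% | 50.2% |

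More pairs make this worse, because the shift stays the same while the standard error falls.

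**Step 4: scale.** The planned difference is 5 points. The earlier changes cited in Section 9.2 are 9 to 13% (CD68), 11 to 17% (CD163) and 8 to 10% (CD8), that is 4, 6 and 2 points. These are treatment-associated changes and say nothing about how large an operator effect is. They show only that shifts of 1 to 3 points would not be negligible beside the signals sought.

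**Step 5: what is not reached.** The recommended dose, ORR and the secondary endpoints do not use tissue imaging. The mRNA panel involves no choice of image regions.

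**The case against.** The strongest case on the other side has five parts.

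- *The workflow leaves little room for judgement.* Regions are to cover the whole biopsy, and segmentation, phenotyping and per-cell scoring are done by software. This largely stands: the protocol does not describe a person grading slides by eye. Some discretion remains in placing about 20 fields and in running the software, and masking would close it.
- *Section 6.3 is the usual statement for an open-label trial and is not about the laboratory.* That is a fair reading of its purpose. Taken literally, though, it covers the whole study, and nothing elsewhere in the protocol makes an exception for image analysis. The laboratory may mask in practice, or a document not shown here may require it, but the protocol as worded says the opposite.
- *No bias has been shown.* This stands. The table in the working shows what any paired t-test does under an assumed shift.
- *A prompt reading would precede response.* The on-treatment biopsy at C3D1 falls after two 21-day cycles, about week 6, and the first scheduled scan is at week 9. A slide read at once would usually be read before response is known. The protocol does not say when slides are read, however, and this does not help with time point.
- *Marker hypotheses 4 to 6 in Section 9.1 predict no correlation with response.* An operator favouring the hypotheses would therefore not create an association there. This stands, and the argument about expected direction applies to hypotheses 2 and 3 only.

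Three stronger readings are tempting and should not be drawn. Section 2.2.2 says "it is an inconsistent method (inherent subjectivity of interpreting results and results are dependent on the antibody used", but that is about qualitative EGFR IHC as a way to select patients for anti-EGFR therapy, not about IHC in general or this imaging assay. The inForm steps should not be described as manual reading. And Section 10.1.3 does not say whether sample codes reveal visit or response, so nothing can be concluded from them either way.

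**Conclusion.** The point holds as an inexpensive improvement, not as a demonstrated error. The protocol specifies no masking of the imaging operator to time point or response, and its only statement on blinding is that there is none. A systematic handling difference could therefore bias the uncontrolled paired analysis that sizes Cohort A, and the exploratory responder comparison.

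The size of any bias is unknown. The false-positive rates of 8.8%, 20.8% and 40.4% rest on assumed shifts of 1, 2 and 3 points, no true change, 18 pairs and an SD of 7. A reader might infer that the before/after or responder differences will be produced by the operator, but the protocol does not support that. It supports only that such a bias is possible and is not guarded against. The trial's primary and secondary conclusions are untouched.

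**What to change.** In Sections 6.3 and 8.2.6, state that although treatment is open-label:

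- tissue slides from both time points are coded in random order before regions are selected;
- the imaging operator and any IHC scorer are masked to time point and response;
- scores are locked before they are linked to visit and response data.

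The cost is relabelling slides that are already coordinated centrally and imaged through one shared resource. No extra reader, visit, biopsy or patient is needed, and the power calculation does not change. The drawback is that slides are read in batches rather than as they arrive. The rule should be in place before reading starts, because masking can be restored afterwards only by re-reading the slides.

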**Exploratory endpoints:**

1. Objective response rate (ORR, per iRECIST), disease-control rate (DCR, per iRECIST), duration of response (DOR, per iRECIST), and progression-free survival (PFS, per iRECIST)
2. Change in pre- and post-treatment levels and activation of immune cells in the peripheral blood and tumor microenvironment
3. Change in pre- and post-treatment mRNA expression in a panel of immune-related genes in tumor tissues
4. Objective response rate (by RECIST v1.1 and iRECIST) according to change in pre- and post-treatment levels and activation of immune cell in the peripheral blood and tumor microenvironment
5. Objective response rate (by RECIST v1.1 and iRECIST) according to pre-treatment PD-L1, EGFR, and CD47 tumor expression by immunohistochemistry

6. Objective response rate (by RECIST v1.1 and iRECIST) according to tumor mutational burden (TMB)

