### Exploratory Hypotheses:

1. Evorpaccept (ALX148), cetuximab, and pembrolizumab will demonstrate improved objective response rate (ORR), disease-control rate (DCR), duration of response (DOR, and progression-free survival (PFS) per iRECIST compared to historical controls
2. After treatment with evorpaccept (ALX148), cetuximab, and pembrolizumab, there will be an enhanced immune response in the peripheral blood and tumor tissue compared to pre-treatment
3. Immune profiles in patients with an objective response to evorpaccept (ALX148), cetuximab, and pembrolizumab will show enhanced immune response in the tumor and peripheral blood compared to non-responders (by RECIST v1.1 and iRECIST)
4. Objective response rate will not correlate with pre-treatment PD-L1 tumor expression by immunohistochemistry (by RECIST v1.1 and iRECIST)
5. Objective response rate will not correlate with pre-treatment EGFR tumor expression by immunohistochemistry (by RECIST v1.1 and iRECIST)
6. Objective response rate will not correlate with pre-treatment CD47 tumor expression by immunohistochemistry (by RECIST v1.1 and iRECIST)
7. Objective response rate will be higher for patients with high tumor mutational burden (TMB, >10 mut/Mb) than for patients with low TMB (<10 mut/Mb) (by RECIST v1.1 and iRECIST)

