#### 9.4.8 EXPLORATORY ANALYSES

Analyses of ORR, DCR, DOR, and PFS per iRECIST compared to historical controls will be performed in a similar manner as described in Sections 9.4.2 and 9.4.3.

The change in pre- and post-treatment immune cells in the tumor microenvironment as measured by nine-color multispectral imaging will be evaluated using a paired t-test. The pre-treatment means, post-treatment means, mean difference between the pre- and post-treatment tumor infiltrating scores, and the 95% confidence intervals will be reported. A sample size of 18 achieves 81% power to detect a mean of paired differences of 5% with an estimated standard deviation of differences of 7% with a significance level (alpha) of 0.05 using a two-sided paired t-test. To account for non-evaluable biopsy specimens or patient dropout, the size of the Cohort A will be 23.

Additional exploratory analyses will be performed as sample size allows.

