**2.3 Target Lesions.** When more than one measurable tumor lesion is present at baseline all lesions up to a maximum of 5 lesions total (and a maximum of 2 lesions per organ) representative of all involved organs should be identified as target lesions and will be recorded and measured at baseline. Target lesions should be selected on the basis of their size (lesions with the longest diameter), be representative of all involved organs, but in addition should be those that lend themselves to reproducible repeated measurements. Note that pathological nodes must meet the criterion of a short axis of  $\geq 15$  mm by CT scan and only the short axis of these nodes will contribute to the baseline sum. All other pathological nodes (those with short axis  $\geq 10$  mm but  $< 15$  mm) should be considered non-target lesions. Nodes that have a short axis  $< 10$  mm are considered non-pathological and should not be recorded or followed (see 8.2.4). At baseline, the sum of the target lesions (longest diameter of tumor lesions plus short axis of lymph nodes: overall maximum of 5) is to be recorded.

After baseline, a value should be provided on the eCRF for all identified target lesions for each assessment, even if very small. If extremely small and faint lesions cannot be accurately measured but are deemed to be present, a default value of 5 mm may be used. If lesions are too small to measure and indeed are believed to be absent, a default value of 0 mm may be used.

**2.4 Non-target Lesions.** All non-measurable lesions (or sites of disease) plus any measurable lesions over and above those listed as target lesions are considered non-target lesions. Measurements are not required but these lesions should be noted at baseline and should be followed as “present” or “absent”.

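### Tissue markers are related to efficacy only through objective response: about 3 responders are expected in 18–23 biopsy pairs, and non-significance could not support the no-correlation hypotheses

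*Protocol*

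**What the plan says.** - **Section 8.2.6, nine-color multispectral imaging:** after the within-patient pre/post comparison, "The pre- and post-treatment biopsies will also be compared between patients that respond to treatment and patients that are refractory to treatment". The mRNA paragraph (770 genes) repeats the split and adds a link between baseline signatures and response.
- **Section 3, exploratory endpoints 4 to 6:** each is an objective response rate by marker, for example "Objective response rate (by RECIST v1.1 and iRECIST) according to pre-treatment PD-L1, EGFR, and CD47 tumor expression by immunohistochemistry".
- **Section 3, exploratory objectives 4 and 5:** these concern the relation of PD-L1, EGFR, CD47 and TMB to efficacy, a wider term.
- **Section 9.1, exploratory hypotheses 4 to 6:** each predicts no correlation, for example "Objective response rate will not correlate with pre-treatment EGFR tumor expression by immunohistochemistry". No bound is given for how small an association counts as none.
- **Section 9.4.8:** "A sample size of 18 achieves 81% power to detect a mean of paired differences of 5" percent; after allowance for losses, "the size of the Cohort A will be 23". This is the only power figure for a biomarker analysis, and it belongs to the within-patient test.
- **Section 8.2.6, peripheral blood:** the mass-cytometry parameters are to be correlated with ORR, PFS and OS.
- **Appendix 2, section 2.3:** after baseline, "a value should be provided on the eCRF for all identified target lesions for each assessment".

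**The concern.** Objective response cuts a continuous measure, the change in the target-lesion sum, at a 30% decrease. That cut is conventional for the primary endpoint. For relating markers to efficacy in a small biopsy cohort it discards most of the information, because few patients are expected to fall on the responder side.

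Two things are at stake. First, patients in Cohort A accept two biopsies, and section 2.3.2 justifies them partly by the search for biomarkers of response and resistance. A comparison resting on about three responders will often miss a real association. Second, hypotheses 4 to 6 predict a null result, so an analysis with low power will tend to look like confirmation. Hypothesis 5 also sits awkwardly with section 2.2.4, which says that the immune-mediated effects of cetuximab may correlate with EGFR expression and that this will be explored.

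**Working it through.** **1. The plan's own figure.** Inputs from section 9.4.8: 18 pairs, mean difference 5%, "an estimated standard deviation of differences of 7" percent, "with a significance level (alpha) of 0.05 using a two-sided paired t-test". Standardised effect 5/7 = 0.714; noncentrality 0.714 × √18 = 3.03 on 17 df. Power is 81.5%, against 81% stated. The figure reproduces and does not depend on the number of responders.

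**2. Expected responders.** The ORR of 15% is from section 9.2.
- 18 × 0.15 = 2.7; 23 × 0.15 = 3.45; 48 × 0.15 = 7.2.
- P(0 or 1), n = 18: 0.85^18 + 18 × 0.15 × 0.85^17 = 0.054 + 0.170 = 0.224.
- P(0 or 1), n = 23: 0.85^23 + 23 × 0.15 × 0.85^22 = 0.024 + 0.097 = 0.120.

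**3. Power of responder versus non-responder.** The protocol gives no effect size or test for this comparison. I assume a two-sided 0.05 two-sample t-test with noncentrality d / √(1/n1 + 1/n2).
- 3 v 15: √(1/3 + 1/15) = 0.632. With d = 0.714, noncentrality is 1.13 and power 19%. For 80% power, d must be about 1.9.
- 3 v 20: power 20% at d = 0.714. For 80% power, d must be about 1.8.
- Averaged over the binomial responder count (fewer than 2 counted as no rejection): 15% (n = 18) and 20% (n = 23) at d = 0.714; 25% and 34% at d = 1.

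**4. Baseline immunohistochemistry.** Section 4.1.4 obtains archival tissue, when available, in both cohorts, so the sample could approach 48 (an upper limit). With 7 v 41, power at d = 0.714 is 40%. The 95% CI half-width is 2.01 × √(1/7 + 1/41) = 0.82 SD, so a non-significant result would leave large differences open.

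**5. The same patients with a continuous outcome.** Simulation, 20,000 trials per cell. Marker and tumor change are assumed bivariate normal with correlation rho, responders are the best 15%, and the split uses a pooled t-test.

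| n | rho | Responder split | Spearman |
|---|---|---|---|
| 18 | 0.4 | 16% | 34% |
| 18 | 0.5 | 24% | 52% |
| 18 | 0.6 | 33% | 72% |
| 23 | 0.4 | 21% | 44% |
| 23 | 0.5 | 32% | 65% |
| 23 | 0.6 | 44% | 83% |
| 48 | 0.3 | 26% | 50% |
| 48 | 0.4 | 44% | 78% |
| 48 | 0.5 | 63% | 94% |

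In the pairs the gain runs from 34 − 16 = 18 to 72 − 33 = 39 points. A second run agreed within about 2 points.

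**6. Sensitivity to ties.** Section 9.2 assumes DCR 65%, so 35% lack disease control. Suppose (an assumption) that this 35% is tied at the worst rank, with n = 18 and rho 0.5. If they are the patients with most target growth, the comparison is 24% v 50%. If their rank is unrelated to target change, it is 24% v 23–24% and the gain vanishes.

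**7. Limits of the better measure.** The approximate 95% CI around a correlation of zero is ± tanh(1.96/√(n − 3)): ±0.47 (n = 18), ±0.41 (n = 23), ±0.28 (n = 48).

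**The case against.** The analyses are exploratory, the SAP is not shown, and method detail normally belongs there. Section 9.4.8 allows further exploratory analyses as sample size permits, and nothing excludes percentage change. Exploratory objective 3 itself speaks of response, so the gap between objective and endpoint concerns objectives 4 and 5 only. All this limits the weight of the point. It does not remove it, because the endpoints, the tissue comparison and the no-correlation hypotheses are fixed in the protocol.

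A reader might infer more than the documents support:
- **That the 18 to 23 pairs are the sample for hypotheses 4 to 6.** They are not. Those hypotheses concern pre-treatment expression, and archival tissue can extend the sample to both cohorts.
- **That no association could be found.** Power is low, not absent; differences of about 1.8–1.9 SD are detectable with 80% power.
- **That every biomarker analysis is affected.** The mass-cytometry blood parameters also use PFS and OS, and the paired pre/post test is sound.
- **That the plan treats non-significance as confirmation.** No passage says so, and section 9.4.1 provides 95% confidence intervals for exploratory outcomes generally. The weakness is that the hypotheses predict a null without saying how it would be judged.

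It is also fair that a continuous outcome would not prove absence of correlation. Ranking every patient with a new lesion as worst would conflict with the iRECIST rationale in Appendix 2 that new lesions may not be true progression. The fix therefore avoids that rule.

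**Conclusion.** The point holds for the tissue marker–efficacy analyses. At ORR 15% the pre/post comparison expects about 3 responders and has roughly 15–35% power for differences of 0.7 to 1 SD. Hypotheses 4 to 6 could not be supported by a non-significant test even with 48 patients and about 7 responders, and hypothesis 5 needs reconciling with section 2.2.4.

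The gain of roughly 20–40 points from percentage change rests on bivariate normality, correlations of 0.4–0.6 and few ties at the worst rank. It is a favorable case and can shrink to nothing. The finding is confined to exploratory objectives; primary and secondary conclusions are untouched.

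**What to change.** - **Section 8.2.6, exploratory endpoints 4 to 6 and section 9.4.8:** add a rank (Spearman) correlation between each tissue marker, or its change, and best percentage change from baseline in the sum of target-lesion diameters. Report the estimate with its 95% CI beside the responder comparison, which stays.
- **Ranking:** patients with no post-baseline scan because of death or deterioration take the worst rank. Patients with new lesions keep their measured target change. A sensitivity analysis gives the worst rank to confirmed progression (iCPD).
- **Section 9.1:** reword hypotheses 4 to 6 so that they are judged by the estimated association and its CI, and reconcile hypothesis 5 with section 2.2.4.

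The cost is wording and one variable derived from lesion values already on the eCRF; no patients, scans or samples are added. Inclusion criterion 9 says that lesions to be biopsied should not be target lesions, so biopsy should not distort the sum. The downside is that target change ignores non-target and new lesions, which the responder display and the sensitivity analysis cover.
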